## Abstract

**CLINICAL TRIAL REGISTRATION:**

The study is registered on the official website of ClinicalTrials.gov

**IDENTIFIER:**

ID NCT 05961813

## INTRODUCTION

The global tobacco epidemic still causes 8 million deaths each year^1^. Smoking is a risk factor for premature death and disability^2^, and is a major risk factor in all kinds of surgery^3^. Smoking is associated with high mortality^4^ and an increased risk of general morbidity^5^ which may lengthen hospital stay, raise readmission rates and ultimately increase healthcare costs^6^.

It has been shown that tobacco consumption poses a particularly significant risk in several surgical specialties^7^. Specifically, in colorectal surgery, smokers have a 30% higher risk of mortality and morbidity after colorectal resection than people who have never smoked or are ex-smokers^8^. In urinary tract surgery, the risk of post-surgical complications after radical cystectomy is almost twice as high in smokers, particularly wound dehiscence and myocardial infarction^9^, and after radical prostatectomy smokers present a higher risk of pneumonia and unplanned intubation requirement^10^. In the field of orthopedic surgery, smokers have a higher than average rate of bone mineral loss, and their fractures take longer to heal^11^. One systematic review concluded that smoking significantly increases periprosthetic intra-articular space infection and surgical wound complications in primary hip and knee joint replacement surgeries^12^.

Quitting smoking before surgery reduces surgical complications and provides benefits in the short-, medium- and long-term^13^. Clinical trials have shown that offering help to stop smoking before surgery encourages smoking cessation, reduces the risk of cardiovascular complications and surgical wound infection, and helps to shorten hospital stay^14^.

Most smoking treatment guides, including the one published by the US Public Health Services^15^, recommend the 5 As brief intervention model, which comprises five steps or actions: 1) Ask, 2) Advise, 3) Analyze, 4) Assist, and 5) Agree on follow-up. In addition, intensive interventions should be incorporated that provide psycho-educational/behavioral support, pharmacological therapy^15^ and follow-up visits for approximately one year to prevent relapses^16^. In the context of surgery, previous studies have shown that multi-component intensive interventions with sessions starting before surgery and followed up over time achieve the highest rates of abstinence^14,17^.

According to the Spanish Ministry of Health’s Survey on Alcohol and Drugs, 33.1% of the country’s population aged ≥15 years still smokes^18^. Smokers are likely to suffer from chronic and acute tobacco-related pathologies, and generate high economic and social costs for the country’s health system^19^. Many will need surgery to treat medical conditions that may or may not derive from their tobacco use.

The need to undergo surgery is associated with a higher probability of successful smoking cessation^20^. But in spite of the opportunity that imminent surgery represents for giving up smoking, tobacco consumption in the pre-surgical period is not an issue that is systematically addressed13. In Catalonia, the identification of smokers who are motivated to give up (and the provision of support for their efforts to do so) does not reach the desired levels^21^. It is clear that effective interventions should be planned at key times such as pre-surgical visits.

The World Health Organization (WHO) urges countries to include smoking cessation programs for pre-surgical patients^22^ as a measure to reduce complications and improve long-term health. In Spain, however, there is no systematic pre-surgical intervention for cessation of tobacco use, nor has any such intervention been evaluated to date. According to the WHO’s ‘Research on the Implementation of Health Policies: a Practical Guide’^23^, applied research is needed to evaluate the effectiveness of interventions, taking into account the real situations of healthcare systems and patients. Conducting studies that demonstrate not just the effectiveness of interventions but also the feasibility of their introduction into real healthcare systems favors their subsequent implementation, sustainability, and dissemination.

The aim of the trial described here is to evaluate the efficacy of an intensive pre-surgical intervention to promote smoking cessation in smokers scheduled to undergo either elective orthopedic surgery with implants or general/urological surgery. These types of surgeries provide sufficient time for preoperative planning and the implementation of a smoking cessation intervention (4 weeks), enabling us to compare the impact across various surgical types and highlight potential differences in outcomes.

The primary outcome is tobacco use (Yes/No, defined as active use in the last 7 days) and the secondary outcome is the presence of surgical complications (classified into respiratory, cardiovascular, wound complications, and mortality).

The specific objectives are the following:

To compare the effectiveness of the intervention in terms of abstinence, patient evolution, motivation and the attempts to quit smoking between the patients in the IG and the CG undergoing one of the two types of surgery.To compare the length of hospital stay (in days) and the number of re-admissions between the IG and the CG according to type of surgery.To compare surgical and post-surgical complications and mortality rates between the IG and the CG up to 90 days post-surgery.To assess whether the intervention can be implemented in the health system in Spain.

These objectives will be analyzed by comparing the results obtained in the IG and CG at the following time points: before surgery (at the beginning of the study), on the day of surgery, and at 1, 3, 6 and 12 months post-surgery (Table 1).

**Table 1 t0001:** Plans for assessment and collection of different variables in surgical patients who participate in the RCT at the Vall d´Hebron University Hospital, Barcelona (N=232)

*Variables*	*Baseline*	*Day of* *surgery*	*1 month* *post-surgery*	*3 months* *post-surgery*	*6 months* *post-surgery*	*12 months* *post-surgery*	*Re-admission*
Sociodemographic data	x						
Specialty	x						
Type of SI	x						
Smoker (yes/no)	x	x	x				
Type of consumption	x						
Amount of consumption	x	x	x (if s)	x (if s)	x (if s)	x (if s)	
Fagerström test	x		x (if s)	x (if s)	x (if s)	x (if s)	
Stages of change	x		x (if s)	x (if s)	x (if s)	x (if s)	
Richmond test	x		x (if s)	x (if s)	x (if s)	x (if s)	
Previous abstinence	x						
Previous drugs	x						
Living with smoker	x						
Comorbidities	x						
General self-efficacy scale	x						
CO-oximetry		x					
ASA PS classification		x					
ATB prophylaxis		x					
Duration of surgery		x					
Blood transfusion		x					
SatO2 at start of surgery		x					
Complications of surgery		x					
Complications at time of recovery room care discharge after surgery		x					
Attempts to quit			x (if s)	x (if s)	x (if s)	x (if s)	
Decrease in consumption			x (if s)	x (if s)	x (if s)	x (if s)	
Pharmacological treatment			x	x	x	x	
Is lack of NRT funding a problem?			x	x	x	x	
Readmission (yes/no)							x
Reason for readmission							x
SSI							x
Postoperative mortality							x

RCT: randomized clinical trial. SI: surgical intervention. ASA PS: American Society of Anesthesiologists physical status scale. ATB: antibiotic. SatO2: oxygen saturation. NRT: nicotine replacement therapy. SSI: surgical site infection. if s: if smokes.

## METHODS

The SPIRIT 2013 RCT protocol reporting guide was used^24^ (see Supplementary file), this study is a stratified randomized clinical trial (RCT) with two intervention groups (IG) and two control groups (CG) (n=58 per group) of smokers scheduled to undergo either orthopedic surgery with implants or general/urological surgery. Subjects will be followed up to 12 months after surgery.

### Study population

The study population will be adult patients scheduled to undergo the following surgeries at the Orthopedic Surgery and Traumatology, General Surgery and Urology services at the Vall d’Hebron University Hospital in Barcelona: knee replacement, hip replacement, instrumented spinal arthrodesis, anterior cruciate ligament repair, colorectal surgery for colon and rectal neoplasia, cystectomy, radical prostatectomy and partial or radical nephrectomy. The inclusion criteria are: adults aged ≥18 years; conscious and oriented in space, time and person; scheduled for surgery at least four weeks after inclusion in the surgical schedule; daily and occasional smokers (occasional: do not smoke every day); resident in the healthcare area and have no plans to change address in 12 months. The exclusion criteria are: pregnancy; smokers already undergoing treatment to stop smoking; inability to give informed consent due to memory loss or insufficient understanding of Spanish or Catalan; non-primary nature of knee or hip replacement; scheduled to participate (or already participating) in a clinical trial in which nicotine replacement therapy (NRT) is an exclusion criterion.

### Sample size and randomization

Every year, approximately 1800 surgical procedures of these kinds are performed at our hospital, of which approximately 25% are carried out in smokers. The sample size has been calculated assuming four equal groups with an estimated difference of 15 percentage points between the predicted rates of abstinence at twelve months in the IG (20%) and the CG (5%). With an expected loss to follow-up rate of 10%, 232 subjects will be needed (58 per group). The sample size has been calculated using the software STATA (StataCorp. 2023. *Stata Statistical Software: Release 18*. College Station, TX: StataCorp LLC). Patients will be assigned to their group by computer-generated random sequence (Stata *ralloc* function) (1:1 assignment) (REDCap). The study will be conducted in a single-blind manner (blinded for surgeons, collaborating researchers, and outcome analysts). There are no circumstances that would necessitate unblinding.

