### Outcome variables

The main outcome variable will be tobacco use (Yes/No, defined as active use in the last 7 days)^25^ at the various time points. Abstinence validation will be performed with CO-oximetry on the day of surgery and at 12 months for subjects who declare themselves abstinent (patients with CO >6 ppm will be considered as active smokers)^26^. At the other time points (start of the study, and at 1, 3, 6 and 12 months) abstinence will be self-reported by the patient. The following secondary variables will be recorded at each assessment: 1) type of tobacco product (cigarettes, rolling tobacco, cigars, etc.); 2) pattern of consumption of each type of tobacco product (daily or occasional, and daily/weekly amount); and 3) level of nicotine dependence, using the Fagerström test (low 0–3, medium 4–6, and high 7–10)^27^. Other variables that will be assessed include motivation and self-efficacy, willingness to quit smoking according to the Prochaska and Di Clemente model^28^, level of motivation using the Richmond test^29^; and the General self-efficacy scale (based on Bandura’s social cognitive theory)^30^.

Another outcome variable will be surgical complications classified into the following groups and assessed on the day of surgery, on discharge from recovery-room care, hospital discharge, and up to 90 days post-surgery: 1) respiratory complications (bronchospasm, respiratory failure requiring oxygen and active treatment, respiratory superinfection requiring antimicrobial treatment, pleural effusion, other); 2) cardiovascular complications (deep venous and pulmonary thromboembolic disease, hypertensive crises, angina, new onset arrhythmias/blockages, acute myocardial infarction, heart failure, other); 3) postoperative complications of the surgical wound (dehiscence, fistula or infection of the internal or deep wound, seroma, wall abscess or fistula of the external wound with antimicrobial treatment and positive cultures, other); and 4) mortality (during hospitalization and within 90 days of surgery). All complications after the day of surgery will be recorded taking into account data from the patient’s medical history. Variables related to surgery: surgical time, blood transfusions (to be assessed as possible confounding variables for post-surgical complications and mortality). Variables related to hospital care: length of hospital admission (in days); and readmissions required within 12 months of hospital discharge.

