### Procedure

This pragmatic intervention will be carried out at different hospital services and will involve healthcare professionals from different ambits for evaluation. The intervention will begin in the pre-surgical period, at the pre-anesthetic visit, where smokers who meet the inclusion criteria outlined in the protocol will be invited to participate. Those who agree will receive more detailed explanations of the nature of the study and they will be asked to provide written informed consent. An information leaflet (see Supplementary file) will be provided to all patients who agree to take part. Within 24–48 hours they will receive a telephone call during which baseline data will be recorded, and at the end of the interview, patients will be randomly assigned to the IG or the CG. Participants will receive the following, according to their group.

*Intervention group (IG)*

Intensive intervention consisting of two pre-surgical visits starting at least four weeks before surgery (depending on the type of surgery) + an information leaflet (see Supplementary file) + pharmacological therapy (NRT if needed) + four follow-up consultations by telephone, carried out by expert staff trained in intensive smoking interventions (at 1, 3, 6 and 12 months after surgery) with the aim of maintaining abstinence.

*Control group*

A single visit with brief advice to stop smoking and the same information leaflet between three and six weeks before surgery (depending on the type of surgery) provided by healthcare personnel. Follow-up after discharge will be by telephone at 1, 3, 6 and 12 months after discharge, but no more advice will be given.

The intervention procedure is detailed in Figure 1.

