**Follow-up visits** By phone after surgery	Assessment of self-reported abstinence. Assessment of treatment adherence and difficulties in following it. Reinforcement of behavioral strategies to cope with smoking urges. Relapse prevention. Recording data on tobacco use and variables if the patient continues to smoke. Measurement of CO-oximetry at the end of the study. Prompt notification of patients who do not attend, so as to try to arrange visits as soon as possible.

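### The stated single blind does not reach abstinence assessment: in the intervention arm tobacco use is recorded by arm-aware staff within the counselling call, and at 1, 3 and 6 months nothing but self-report stands behind it

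*Protocol article*

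**What the plan says.** **Blinding.** Under Sample size and randomization: "The study will be conducted in a single-blind manner (blinded for surgeons, collaborating researchers, and outcome analysts". Patients, counsellors and follow-up interviewers are not in that list. The Limitations section names single blinding as a limitation and gives no remedy for outcome assessment.

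**Outcome.** Under Outcome variables: "The main outcome variable will be tobacco use (Yes/No, defined as active use in the last 7 days", assessed at several time points. On its source: "At the other time points (start of the study, and at 1, 3, 6 and 12 months) abstinence will be self-reported by the patient". On its validation: "Abstinence validation will be performed with CO-oximetry on the day of surgery and at 12 months for subjects who declare themselves abstinent"; a reading above 6 ppm counts as smoking.

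**Intervention-arm calls.** Under Procedure, this arm receives "carried out by expert staff trained in intensive smoking interventions (at 1, 3, 6 and 12 months after surgery) with the aim of maintaining abstinence". Components of the intensive intervention describes the intervention staff as tobacco-addiction experts of the hospital's Preventive Medicine service. Table 2 lists what the post-surgery calls contain: abstinence assessment, coping reinforcement, relapse prevention and, in the same list, "Recording data on tobacco use and variables if the patient continues to smoke".

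**Control-arm calls.** Under Procedure, controls are telephoned at 1, 3, 6 and 12 months, "but no more advice will be given". The caller is not identified.

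**Use of the data.** Data analysis plans logistic regression for efficacy and a binomial mixed model over the repeated assessments for the evolution of cessation.

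**The concern.** The main outcome is a patient's answer to a question. In one arm the question belongs to a treatment session run by someone who knows the allocation and has been coaching the patient to stop. In the other it is put in a call with no treatment content. A patient who is still smoking may answer differently in these two settings, and an arm-aware recorder may treat a doubtful answer differently. Blinded analysts cannot undo this, because the data reach them already shaped by unblinded patients and staff.

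At stake are the arm comparisons at 1, 3 and 6 months and the mixed model, for which those three visits supply most of the post-surgery data. An apparent early effect, or an apparent difference in trajectory, could be partly a measurement effect. Because the procedure differs by arm in the protocol itself, no later analysis plan can remove the problem.

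**Working it through.** **Step 1. Who obtains the answer, and with what check.**

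| Time point | Intervention arm | Control arm | CO check |
|---|---|---|---|
| Day of surgery | recorder not stated | recorder not stated | yes, for declared abstainers |
| 1, 3, 6 months | intervention staff, within the counselling call | no-advice call, caller not named | none |
| 12 months | intervention staff, within the counselling call | no-advice call, caller not named | required in Outcome variables, but see step 2 |

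Staff who deliver the intervention necessarily know the arm. The problem is therefore shown at 1, 3, 6 and 12 months, is unchecked at 1, 3 and 6 months, and is not shown for the day of surgery.

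**Step 2. Is the 12-month check firmly fixed?**
- Outcome variables requires CO at 12 months for declared abstainers, then includes 12 months among the self-reported times.
- Table 1 marks CO-oximetry on the day of surgery only.
- Table 2 lists an end-of-study CO measurement, but among the components of telephone visits and in a table that describes only the intensive intervention.
- The Discussion assumes CO readings on the day of surgery and at study end.

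The intention is clear enough. The passages do not agree, and only the general wording in Outcome variables carries the check to the control arm.

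**Step 3. How far could the difference move?** The article gives no misreporting rate, and no expected abstinence rates for 1, 3 or 6 months. The 12-month design rates are borrowed purely as an illustration.

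Inputs: true abstinence 20% (intervention) and 5% (control), from Sample size and randomization, so 80% and 95% still smoke. Assumptions: a share r of control smokers and r + e of intervention smokers are wrongly recorded as abstinent.

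- Observed intervention rate = 0.20 + 0.80(r + e)
- Observed control rate = 0.05 + 0.95r
- Observed difference = 0.15 + 0.80e − 0.15r
- Shift from the true difference, in percentage points = 80e − 15r (r and e as proportions)

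| Excess e | r = 0 | r = 5% | r = 10% |
|---|---|---|---|
| 5% (4 − 15r) | 4.0 | 3.25 | 2.5 |
| 10% (8 − 15r) | 8.0 | 7.25 | 6.5 |

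The r = 0 column is the largest shift for each excess. With e = 0 the shift is −15r, so equal over-reporting would shrink the difference slightly. It is the excess in one arm that inflates it.

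**Step 4. What if there were no true effect?** Take 5% true abstinence in both arms, no over-reporting by controls, 10% loss (58 × 0.90 ≈ 52 per group, or 104 per arm with both surgery types pooled), and a two-sided two-proportion z-test at 0.05.

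| Excess e | Spurious difference = 0.95e | P(reject), 52 per arm | P(reject), 104 per arm |
|---|---|---|---|
| 2% | 1.9 points | 0.07 | 0.09 |
| 5% | 4.75 points | 0.15 | 0.26 |
| 10% | 9.5 points | 0.37 | 0.64 |

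These probabilities describe a comparison without CO validation.

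**The case against.** **The plan never says that counsellors are blinded.** This is correct. A reader might infer that the blinding sentence is contradicted by Table 2. It is not: the sentence names three groups, and nothing identifies the counsellors with any of them. The fault is that the statement leaves abstinence assessment uncovered without saying so.

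**CO validation protects the endpoint.** Largely true where it is done. The 20% v 5% rates belong to 12 months, where Outcome variables calls for a CO check. A reader might therefore take 4 or 8 points as bias in the 12-month result, or as a fraction of the 15-point target that is lost. The documents do not support that. The check gives no protection at 1, 3 and 6 months, it does not make the assessment blind, and the passages on it at 12 months conflict.

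**Controls may over-report too.** They receive advice to quit and the same leaflet, so inflation confined to the intervention arm is not documented. Nor is it documented that a different person calls controls, or that counsellors would shade an answer. What is documented is that the content of the call differs by arm. Step 3 allows for over-reporting by controls.

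**Abstinence may already be asked first.** Table 2 puts its assessment at the head of the list, but a list of components is not a stated sequence. Scripts and caller roles may well be set out in a fuller protocol. Their absence from an article is not the point; the placing of outcome recording inside the treatment call is.

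**A separate blinded caller is costly and incomplete.** It could mean up to 116 × 4 = 464 extra contacts in a trial that already recruits slowly. Patients would still know their arm, so interviewer bias would be reduced but not self-report bias. This stands, and it is why the fix does not depend on such a caller.

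**Conclusion.** The concern holds within limits. In the intervention arm, arm-aware staff record the main outcome within the counselling call at 1, 3, 6 and 12 months, while controls are asked in a call without advice. The single blind does not extend to this assessment. At 1, 3 and 6 months, where self-report stands alone, the arm comparison and the mixed model are open to differential misreporting.

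The size cannot be derived from the article. Under assumed excess over-reporting of 5% or 10%, over-reporting by controls of 0 to 10%, and the 12-month design rates used only as an illustration, the difference would shift by 2.5 to 4.0 points or by 6.5 to 8.0 points. CO validation should make this smaller wherever it is carried out. The finding does not show that the CO-validated results are biased, and it says nothing about who assesses abstinence on the day of surgery.

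**What to change.** 1. In both arms, ask the 7-day tobacco question at the start of each follow-up call with one fixed script, before any counselling. Where existing staff allow, have it asked by a researcher who is blinded to arm and does not counsel.
2. Rest the efficacy conclusion on the CO-validated time points (day of surgery and 12 months). Report the 1-, 3- and 6-month results, and the mixed model that uses them, as supportive and as unblinded self-report.
3. State under Sample size and randomization that the blind does not cover abstinence assessment.
4. Reconcile Table 1, Outcome variables and Table 2 so that CO validation at 12 months plainly applies to declared abstainers in both arms.

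**Cost.** Items 2 to 4 are wording, and they bring a more modest claim at the intermediate time points. Item 1 is a small change to the call procedure. Only its optional part, the separate blinded caller, could need extra contacts, and it would not remove bias that comes from patients knowing their arm. The article reports 25 of 232 patients recruited, so at that stage most follow-up calls could still be made under the revised procedure.
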